# Rationale and design of PASSAT — patients’ satisfaction with local or general anaesthesia in video-assisted thoracoscopic surgery: study protocol for a randomised controlled trial with a non-randomised side arm

**DOI:** 10.1186/s13063-019-3190-1

**Published:** 2019-02-27

**Keywords:** Patients’ satisfaction, VATS, Thoracic surgery, Psychometrically validated questionnaire, Local anaesthesia, General anaesthesia, Cost effectiveness

## Abstract

**Background:**

Although general anaesthesia (GA) with one-lung ventilation is the current standard of care, minor thoracoscopic surgery, i.e. treatment of pleural effusions, biopsies and small peripheral pulmonary wedge resections, can also be performed using local anaesthesia (LA), analgosedation and spontaneous breathing. Whilst the feasibility and safety of LA have been demonstrated, its impact on patient satisfaction remains unclear. Most studies evaluating patient satisfaction lack control groups or do not meet psychometric criteria. We report the design of the PASSAT trial (PAtientS’ SATisfaction in thoracic surgery – general vs. local anaesthesia), a randomised controlled trial with a non-randomised side arm.

**Methods:**

Patients presenting for minor thoracoscopic surgery and physical eligibility for GA and LA are randomised to surgery under GA (control group) or LA (intervention group). Those who refuse to be randomised are asked to attend the study on the basis of their own choice of anaesthesia (preference arm) and will be analysed separately. The primary endpoint is patient satisfaction according to a psychometrically validated questionnaire; secondary endpoints are complication rates, capnometry, actual costs and cost effectiveness. The study ends after inclusion of 54 patients in each of the two randomised study groups.

**Discussion:**

The PASSAT study is the first randomised controlled trial to systematically assess patients’ satisfaction depending on LA or GA. The study follows an interdisciplinary approach, and its results may also be applicable to other surgical disciplines. It is also the first cost study based on randomised samples. Comparison of the randomised and the non-randomised groups may contribute to satisfaction research.

**Trial registration:**

German Clinical Trials Register, DRKS00013661. Registered on 23 March 2018.

**Electronic supplementary material:**

The online version of this article (10.1186/s13063-019-3190-1) contains supplementary material, which is available to authorized users.

## Background

Video-assisted thoracoscopic surgery (VATS) is the current standard of care for most thoracic operations, ranging from the management of pleural effusions to extended anatomic and oncological radical resections. The standard anaesthetic approach is general anaesthesia (GA) with double-lumen tube and one-lung ventilation (OLV). By inducing a controlled collapse of the non-dependent lung, OLV provides optimal access to the surgical field, especially to “hidden” sites like the mediastinal face of the lung. GA improves surgical conditions, as neuromuscular blockade reduces unwanted diaphragmatic movements, and profound anaesthesia suppresses coughing when central, peribronchial structures are prepared. This setup has enabled modern thoracic surgery since the 1960s [1, 2].

Despite these advantages, GA also has some adverse effects. The collapse of the non-dependent lung and its ventilation-perfusion mismatch are proinflammatory on the alveolar level: lesion of the glycocalyx, increased alveolo-capillary permeability, surfactant dysfunction and alveolar oedema may contribute to the development of acute respiratory distress syndrome (ARDS) [3–6]. Some muscle relaxants can cause an exacerbation of chronic obstructive pulmonary disease (COPD) via histamine release and impaired bronchial constriction [7]. Especially in elderly patients, GA is associated with a high rate of postoperative cognitive dysfunction (POD; 19−30*%*) such as delirium [8–10]. POD leads to longer hospital stays, higher demands for nursing care, medication and mobilisation therapy and significantly higher costs [11].

However, there is no need for profound anaesthesia and OLV in many surgical indications. The minimised access via VATS is predestined for local anaesthesia (LA), i.e. intercostal block, accompanied by analgosedation. The respective indications are the treatment of pleural effusions, biopsies and small peripheral wedge resections. A number of recent studies have evaluated the role of LA in VATS [1, 12–17]. In combination with a laryngeal mask airway and intraoperative vagal block, even extended anatomic lung resections are possible [18, 19]. Of course, this extended approach of “monitored anaesthesia care” (MAC) is even more complex than the standard of care [20].

Indications for LA or GA are mostly determined by the physician, not the patient [21]. The decision may be influenced by available staff resources, the surgeon’s convenience during the operation or financial interests. As LA is considered to be cheaper than GA [22–26], cost pressures in health care systems may lead to increasing use of local or regional anaesthesia. Most existing cost estimations are not based on randomised controlled trials (RCTs), and they arise from different health care systems. Cost studies applicable to the German health care system, which is based on diagnosis-related groups, are scarce.

Although an increasing number of operations in various surgical specialties are being performed on conscious and spontaneously breathing patients, little is known about the influence of the type of anaesthesia on patient satisfaction. Indeed, patient satisfaction is the most neglected aspect in the currently published research on LA vs. GA.

One reason may be that “satisfaction” is challenging to investigate, as there are innumerable influences, for example the patients’ expectations, the treatment outcome, the perceived care and attention of the staff and many other known and unknown variables [27]. Hence, simply asking “Were you satisfied?” is insufficient to measure the differential impact of anaesthesia. A reliable evaluation of patient satisfaction requires multimodal strategies, including the use of validated questionnaires. Two thorough reviews found more than 3000 studies claiming to evaluate patient satisfaction; however, only 73 used instruments which met valid psychometric criteria [28, 29]. Some of these were constructed for special clinical settings, for example paedriatics, obstetrics or local, regional or general anaesthesia, and they were validated for different languages. Among these, only the “ANP” (“Anästhesiologische Nachbefragungsbogen für Patienten”, i.e. “Anaesthesiologic Questionnaire for Patients”) is suitable for our purpose [30].

Apart from the aforementioned physiological and financial aspects, patient satisfaction should be equally considered in clinical decision making. Hence, it must be investigated in a systematic, i.e. randomised controlled manner. PASSAT is the first RCT on this topic using a validated questionnaire and calculating a sufficient sample size, not only for thoracic surgery, but for surgical disciplines in general.

## Materials and methods

### Study objective

The primary objective of PASSAT is to assess the impact of the anaesthetic technique on the satisfaction of patients undergoing minor VATS. The patients are randomised to receive either GA with OLV or LA with analgosedation and spontaneous breathing. Secondary objectives are complication rates, intra- and postoperative carbon dioxide partial pressure, cost and cost effectiveness (Table 1). Furthermore, patients who refuse randomisation are asked to attend the non-randomised, preference-based side arm of the study. Data from the randomised and non-randomised groups will be compared.

**Table 1 Tab1:** Endpoints

1	Primary endpoint: patients’ satisfaction on the anaesthesia related satisfaction scale of the ANP questionnaire
2	Secondary endpoints:
	∙ Complication rates: systemic inflammatory response syndrome (SIRS), postoperative mechanical ventilation, atrial fibrillation, cardiopulmonary resuscitation (CPR)/ cardiac infarction, air leakage > 7 days, re-operation, pneumonia, new chest tube after surgery, pleural empyema, relevant postoperative bleeding, neurological complications, wound infection, chylothorax, renal failure, heparin-induced thrombopenia, pericardial effusion, pulmonary infarction, pulmonary embolism, paresis of the recurrent laryngeal nerve, abdominal complication, peripheral vascular complication, other complication (to be specified), death
	∙ Intra- and postoperative carbon dioxide tension: (1) arterial blood gas analysis: awake, at wound closure, 30 and 60 min after wound closure; (2) end-tidal capnometry: continuous recording during the operation and for 60 min after; (3) peak pCO_2_ during surgery; (4) time to recovery from peak to baseline pCO_2_
	∙ Direct medical costs: expenses for surgery related personnel (physicians and nurses), medication and medical devices, inpatient care, length of hospital stay

### Study design

PASSAT is a monocentric, unblinded, parallel, RCT carried out at the Department of Thoracic Surgery of Private University Witten/Herdecke, located at the Lungclinic Cologne-Merheim, which is one of the largest departments of thoracic surgery in Germany. The trial contains an additional non-randomised, preference-based side arm (Fig. 1).

**Fig. 1 Fig1:**
[figure not shown]
Consolidated Standards of Reporting Trials (CONSORT) flow chart of PASSAT trial

The protocol is described according to the Standard Protocol Items: Recommendations for Interventional Trials (SPIRIT) Checklist for clinical trials (see Additional file 1).

### Patients

Patients with an indication for video-assisted thoracoscopic management of pleural or pericardial effusion, intrathoracic lymph node biopsies or peripheral pulmonary wedge resection are eligible (Table 2). Currently, about 260 VATS for those minor indications are performed at the investigating clinic per year. Operations which are more extensive need more elaborate forms of anaesthesia than simple LA and analgosedation and are therefore not subject to the trial.

**Table 2 Tab2:** Key inclusion criteria

∙ Indication for VATS for
1 Partial pleurectomy
2 Talcum pleurodesis
3 Implantation of permanent pleural catheter
4 Hilar or mediastinal lymph node biopsies
5 Peripheral pulmonary wedge resection
6 Pericardial effusions
∙ Age ≥ 18 years
∙ Eligibility for LA as well as GA
∙ Informed consent

The exclusion criteria ensure that the planned operations will be safely performed in LA with analgosedation (Table 3).

**Table 3 Tab3:** Key exclusion criteria

∙	Systematic lymphadenectomy
∙	Expected difficult airway
∙	Emergent operation
∙	Severe coagulation disorders (partial thromboplastin time, PTT > 40 s; international normalised ratio, INR > 1.5)
∙	Previous ipsilateral radiation or surgery
∙	COPD with severe impairment of pulmonary function: diffusing capacity of the lung for carbon dioxide (DLCO)/alveolar volume (AV) < 30%, forced expiratory volume in 1 s (FEV_1_) < 30%
∙	Pregnancy and lactation

Patients do not receive any compensation.

### Randomisation and preference arms

Eligible patients are randomised with variable block size without stratification to the control (GA) or test group (LA) as shown in Fig. 1. Patients are allocated using the built-in randomisation module of the electronic data capture (EDC) software (see the following section on “Data management and confidentiality”).

Patients who refuse to be randomised are asked to attend the preference arm. They may choose their form of anaesthesia. The preference arm is not limited to a certain sample size. Recruitment ends when the randomised arms achieve the calculated sample size.

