### Hypothesis and sample size calculation

The null hypothesis is that patients with LA are as satisfied with anaesthesia according to the “satisfaction with anaesthesia” score of the ANP as those with GA. The alternative hypothesis is that satisfaction in both groups is not equal. The score is noted on an ordinal scale from 0 to 3. The mean satisfaction in the evaluation study was *μ*=2.58 with a standard deviation of *σ*=0.54 [30]. A difference of satisfaction of *ε*=0.32 point is defined as clinically relevant, resulting in a mid-scale effect size *ε*/*σ*=0.59. With a significance level of *α*=5*%*, a power of (1−*β*)=80*%* and an allocation rate of 1:1, we need 
$$ n=\left(1+\frac{1}{1} \right) * \left(\sigma * \frac{Z_{(1-{\alpha}/{2})} + Z_{(1-\beta)} }{\epsilon}\right)^{2}=45 $$ patients in each randomised group [40]. Since the ANP satisfaction scale is ordinal, we correct the sample size by +10%. Furthermore, we expect a dropout rate of 10%. In summary, 2∗45∗1.1∗1.1=108 patients will be included in the randomisation group of the study.

Statistical analyses will be performed using the statistical language R. Data will be presented using descriptive statistics such as frequency or mean and standard deviation. Individual changes from baseline to the end of treatment will be analysed if appropriate. After checking for normal distribution, the primary endpoint will be tested with Student’s *t* test or the Mann-Whitney *U* test, respectively. There will not be an interim analysis for the primary endpoint. Multivariate analysis will be performed to identify independent variables which then can be the focus of further investigations.

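### The stated primary comparison ignores planned procedure, which is known before randomisation; adjusting for it would give a modest gain in precision and make chance imbalance easier to interpret

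*Protocol article*

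**What the plan says.** Table 2 of the protocol article (Patients) lists six indications, among them "Implantation of permanent pleural catheter" and "peripheral pulmonary wedge resection". The same section limits the range: "Operations which are more extensive need more elaborate forms of anaesthesia than simple LA and analgosedation and are therefore not subject to the trial".

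Under Randomisation and preference arms: "Eligible patients are randomised with variable block size without stratification".

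The indication is fixed before allocation. It is an inclusion criterion, the data-capture system randomises only once the criteria have been checked (Data management and confidentiality), and the surgeon explains the operation before the patient is randomised (Anaesthetic and surgical procedures).

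Hypothesis and sample size calculation gives one method for comparing the arms: a t test or Mann-Whitney test on the ANP score, chosen after a normality check. The hypothesis is two-sided: "The alternative hypothesis is that satisfaction in both groups is not equal". A multivariate analysis is also planned, but its purpose is to find predictors for later research. It names no covariates and is not described as an adjusted LA-versus-GA estimate. The Discussion ties the capnography analysis to preoperative lung function, not to procedure. For cost, length of stay and complications the article states no method.

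**The concern.** The trial pools pleural and pericardial drainage procedures, node biopsies and resection of lung tissue. Planned procedure may well be prognostic, less for satisfaction with anaesthesia than for length of stay, inpatient cost or some Table 1 complications ("air leakage > 7 days, re-operation, pneumonia, new chest tube after surgery"). Unstratified blocks balance the numbers per arm but not the case mix, and neither stated test can take a covariate.

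Two things are at stake. Whatever variance procedure explains stays in the standard error, although it could be removed at almost no cost. And if the arms turn out to differ visibly in case mix, readers will ask whether the result reflects anaesthesia or procedure, with no prespecified adjusted estimate to answer them. The trial is unblinded and the investigators analyse the data, so an adjustment added after an imbalance has been seen would look data-driven.

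**Working it through.** **Inputs from the article:** difference 0.32, SD 0.54, two-sided alpha 5%, power 80%, allocation 1:1, 54 per arm.

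**Assumed, because the article does not give them:** the share p of a procedure group (30-50%), and the share R² of outcome variance that procedure explains (0.02-0.30).

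**1. The plan's own figure.** n = 2 × (0.54 × (1.960 + 0.842) / 0.32)² = 44.7, so 45 per arm. Then 2 × 45 × 1.1 × 1.1 = 108.9, stated as 108, or 54 per arm. The figure reproduces. Power with 45 per arm, that is, with both 10% allowances used up: Φ(0.32 / (0.54 × √(2/45)) − 1.960) = Φ(0.851) = 80.3%.

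**2. Chance imbalance with 54 per arm.** The SD of the between-arm difference in a group's share is about √(2p(1−p)/54).
- p = 0.3: SD 8.8 points; P(difference ≥ 10 points) = 26%.
- p = 0.5: SD 9.6 points; P = 30%.

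Exact hypergeometric probabilities for 32, 43 and 54 of 108 patients are 29%, 24% and 34%. They are not monotone because 10 points is 5.4 patients: the smallest qualifying difference is 6 patients when the group total is even and 7 when it is odd. Overall the probability is roughly a quarter to a third. A difference of 15 points or more has exact probability 6%, 12% and 8%.

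**3. What this does to the unadjusted test.** In outcome SDs, the unadjusted standard error is √(2/54) = 0.192. The part due to procedure imbalance has SD √(2R²/54): 0.043 at R² = 0.05, 0.061 at 0.10 and 0.105 at 0.30. This part is already inside the 0.192; at R² = 0.10, 0.061² + 0.183² = 0.037 = 0.192². Simulation (20,000 runs, six equal procedure groups) gave a type I error of 5.0% at R² = 0.10 and 4.7% at R² = 0.30. The test is valid.

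**4. What adjustment gains.** In a linear model the residual SD is 0.54 × √(1−R²). At R² = 0.10 this is 0.512, so power with 45 per arm is Φ(0.32 / (0.512 × √(2/45)) − 1.960) = Φ(1.003) = 84.2%.

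| Assumed R² | Power, 45 per arm | n per arm for 80% power | CI width relative to unadjusted |
|---|---|---|---|
| 0 | 80.3% | 45 | 1.00 |
| 0.02 | 81.0% | 44 | 0.99 |
| 0.05 | 82.2% | 43 | 0.975 |
| 0.10 | 84.2% | 41 | 0.95 |
| 0.20 | 88.2% | 36 | 0.89 |

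The width ratio √(1−R²) applies equally to continuous secondary outcomes; at R² = 0.30 it is 0.84. The 1-2 degrees of freedom spent are ignored here and are negligible at this size.

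**The case against.** The strongest reply is that nothing in the randomisation section is wrong. Unstratified permuted blocks are valid for 108 patients in one centre, and six strata would be sparse. That stands: omitting stratification is an acceptable choice. Changing it in mid-trial would also be a protocol amendment needing ethics approval, and 27% of the sample was already enrolled in December 2018.

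A reader might infer that a case-mix imbalance would bias the result or pass for an effect of anaesthesia. The documents do not support this. The imbalance is random, its contribution is already in the standard error, and the type I error holds.

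A reader might also infer that no arm comparison in the trial accounts for procedure, including those of cost, stay, pCO2 and complications. The article states no model for these, a full protocol or SAP may supply one, and the capnography analysis already foresees conditioning on lung function. Only the primary comparison can be said to ignore procedure.

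Finally, no section suggests that procedure predicts satisfaction with anaesthesia. The predictors that the article names are anxiety, depression and pain sensitivity, and all operations are minor VATS. This too stands: at R² of 0.05 or less the gain for the primary endpoint is negligible.

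What the reply does not remove is that a baseline variable known for every patient is left out of the one comparison whose method is fixed, and that the multivariate analysis as worded does not fill the gap.

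**Conclusion.** The point holds as a modest matter of precision and interpretability, not as an error that invalidates the analysis. At the planned size, an imbalance of 10 points or more in a large procedure group is quite likely (about a quarter to a third, assuming a share of 30-50%), and the stated analysis has no prespecified answer to it. The gain in primary power is 1-2 percentage points if procedure explains 2-5% of the variance in the ANP score, about 4 points at 10% and about 8 points at 20%. The documents support no particular value. The higher ones are more plausible for cost or length of stay than for satisfaction, which is itself an assumption. The variance formula applies to linear models of continuous outcomes and does not carry over to complication rates.

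**What to change.** Before outcome data are examined by arm:

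- Prespecify planned procedure, as recorded before randomisation, as a covariate in the LA-versus-GA comparison of the ANP score. Pool it into two or three groups. The running text under Patients already suggests three: pleural or pericardial, node biopsy, wedge resection.
- Name one model in advance, for example linear or proportional-odds. The linear model keeps the estimate in score points, the scale of the 0.32 difference; the proportional-odds model gives an odds ratio.
- Keep the unadjusted test as sensitivity analysis.
- Use the same covariate for the continuous secondary outcomes, such as cost and length of stay.
- Use the planned, not the performed, operation, since the latter can change after allocation. Confirm that the database holds the indication as a field; if not, take it from records made before randomisation.

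Leave the randomisation as it is. The cost is 1-2 degrees of freedom, the need to pool rare procedures, and no additional patients. Because the article fixes the primary test, that change probably needs an amendment; the secondary analyses can be settled in the SAP.

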### Data management and confidentiality

All data are entered into a web-based EDC software which is used for data management and is fully compliant with the principles of good clinical practice and all relevant standards of data handling and protection [31]. The EDC contains modules to randomise patients after checking the inclusion and exclusion criteria and to report adverse events. All actions such as edits and changes in the study structure, data collection and study management are saved in the audit trail. Data can only be archived, not deleted. The platform and data are hosted on European servers, and the data are archived for 15 years. The original paper-based research forms will be archived for 10 years. Access to the study data will be restricted, and all appropriate measures will be taken to preserve confidentiality of medical and personal information. Due to the nature of the intervention, blinding is not possible. The data are captured by a study nurse and analysed by the investigators confidentially and pseudonymously.

### Anaesthetic and surgical procedures

All patients are informed in detail about the operation (procedure, risks and alternatives) and the purpose of the study by the surgeon. If the patient agrees, he is randomised to either LA or GA, and the allocation is communicated to the anaesthesiologist, who then informs the patient in detail about the planned anaesthesia.

The following steps apply to both groups: All patients receive midazolam p.o. 1 h before surgery. The surgeon injects mepivacaine at the site of trocars and into the intercostal space in the posterior axillary line. By the end of the operation, piritramide is administered intravenously.

In the LA group, analgosedation via remifentanil and, if necessary, propofol is administered and monitored clinically by the anaesthesiologist and the anaesthesiologic nurse; instrument-based sleep monitoring is not used.

In the GA group, a standard total intravenous anaesthesia with remifentanil, propofol and rocuronium is administered by the anaesthetist and an anaesthesiologic nurse. Neuromuscular monitoring (i.e. train-of-four) is used to assess the level of muscle relaxation.

VATS will be performed via two or three trocars, placed in one or two intercostal spaces, after the trocar site is infiltrated with mepivacaine. If the surgeon needs a mini-thoracotomy to complete the operation or if the operation in LA needs to be interrupted, the patient will be analysed within the original group, according to an intention-to-treat analysis. Interruption criteria are summarised in Table 4.

**Table 4 Tab4:** Criteria for interruption of the operation under LA

∙	Surgical complications: major bleeding, severe adhesions, large tumours, unexpected long operation time
∙	Severe hypoxaemia, pO_2_ < 60mmHg
∙	Severe hypercapnia, pCO_2_ > 80mmHg
∙	Haemodynamic instability
∙	Circumstances hindering the surgeon from preparation: persistent coughing, extensive diaphragmatic movements, insufficient collapse of the lung

The intraoperative monitoring tests are identical in either group: blood pressure, electrocardiography, peripheral O_2_ saturation, end-expiratory carbon dioxide, blood gas analysis. Postoperatively, all patients are monitored at the postoperative care unit before returning to the ward.

